# Sijunzi decoction granules in the prevention and treatment of recurrence of colorectal adenoma: Study protocol for a multicenter, randomized, double-blind, placebo-controlled trial

**DOI:** 10.3389/fphar.2023.1175811

**Published:** 2023-04-05

**Keywords:** traditional Chinese medicine, Sijunzi decoction, randomized controlled trial, colorectal adenoma, spleen deficiency syndrome

## Abstract

**Background:** The recurrence of colorectal adenomas (CRAs) after endoscopy predisposes patients to a risk of colorectal cancer. Guided by the traditional Chinese medicine (TCM), patients with colorectal diseases usually manifest with spleen deficiency syndrome (SDS) and are treated with Sijunzi decoction (SJZD). Therefore, this trial aims to explore the efficacy and safety of SJZD in the prevention and treatment of CRAs recurrence.

**Methods:** SJZD on prevention and treatment of CRAs recurrence after resection: a multicenter, randomized, double-blind, placebo-controlled trial was designed. Patients who undergo polypectomy of CRAs will be recruited and randomized into a SJZD group and a placebo group in a 1:1 ratio. The intervention phase will be 12 months. The follow-up period will last 24 months. The primary outcome is the CRA recurrence rate after intervention. The secondary outcomes include the CRA recurrence rate at the second year post-polypectomy, the pathological type of adenoma and the alterations in SDS scores after intervention.

**Discussion:** Previous clinical practice has observed the sound effect of SJZD in the context of gastrointestinal diseases. A number of experiments have also validated the active components in SJZD. This trial aims to provide tangible evidence for the usage of SJZD, hoping to reduce the recurrence of CRAs.

To counter SDS, our ancestors formulated Sijunzi decoction (SJZD). Since it first appeared in the book “*TaipingHuiminHejiJufang*” in the Song dynasty, SJZD has become a classical prescription in China. It comprises four ingredients: Radix ginseng (Renshen), Rhizoma Atractylodis macrocephalae (Baizhu), Poria (Fulin) and Radix Glycyrrhizae Preparata (Gancao). Chinese researchers have identified that after SJZD intervention, small intestinal peristalsis improved, and abnormal metabolic profiles returned to healthy conditions in an SDS rat model (Zhao et al., 2020). Shi et al. (2019) reported that polysaccharides, an essential extract of SJZD, were conducive to intestinal mucosal restoration, indicating the irreplaceable role of SJZD in treating gastrointestinal diseases. However, few studies have explored the prophylactic effect of SJZD on the recurrence of CRA. Therefore, a randomized, double-blinded, placebo-controlled, and multicenter clinical trial has been designed to investigate the efficacy and safety of SJZD granules in the treatment of patients with SDS after CRA polypectomy.

## Methods and analysis

### Study design and setting

The protocol was approved by the Medical Ethics Committee of Longhua Hospital Affiliated to Shanghai University of TCM (approval number: 2022LCSY031) and was registered in the Chinese Clinical Trial Registry (ChiCTR2200064391) on 6 Oct 2022 (http://www.chictr.org.cn/listbycreater.aspx). The flowchart of this trial is shown in Figure 1.

**FIGURE 1 F1:**
[figure not shown]
The flowchart of the trial.

This is a multicenter, double-blinded, randomized controlled trial (RCT) of two parallel groups. A total of 240 cases will be recruited by recruitment advertisements and introductions from clinicians at outpatient or inpatient departments. Patients who meet the inclusion criteria will be informed of the possibility of participating in this study at the outpatient clinic or at admission. A face-to-face interview will be arranged to inform the patients about the purpose, interventions, examinations and follow-up procedures of this study. After informed consent acquisition, patients will be randomized to the SJZD group or placebo group at a ratio of 1:1. An intervention phase with a 12-month treatment with SJZD granules or placebo will be implemented for recruited patients. Endoscopy will be conducted at the end of the intervention phase and 1 year later. The duration of follow-up is 24 months with 5 visits, and the schedule details are listed in Table 2.

**TABLE 2 T2:** Schedule of trial.

	Period					
Study phase	Enrollment	Visit 1	Visit 2	Visit 3	Visit 4	Visit 5
		3 months of interventions	6 months of interventions	9 months of interventions	12 months of interventions	The second year after intervention
Informed consent form	**√**					
Demographic information	**√**					
Inclusion and exclusion criteria	**√**					
General information	**√**					
Vital signs	**√**	**√**	**√**	**√**	**√**	**√**
Spleen deficiency rating scale	**√**	√	√	√	√	√
Endoscopy	**√**				√	√
Histological tests*	**√**				√	√
Routine blood tests	**√**	√	√	√	√	
Routine urine test	**√**	√	√	√	√	
Routine stool test	**√**	√	√	√	√	
Liver function	**√**	√	√	√	√	
Renal function	**√**	√	√	√	√	
Electrocardiograph	**√**	√	√	√	√	
Serum and stool samples collections	**√**				√	√
Adenomatous tissue collections*	**√**				√	√
Adverse events		√	√	√	√	√
Release drugs/placebo	**√**	√	√	√		
Retrieve empty packages			√	√	√	
Drug combination	**√**	√	√	√	√	√

Notes: Patients who are detected to find recurrence of colorectal adenoma and meet the criteria of resection are undergone endoscopy. Adenomatous tissue will be collected according to the relevant regulations and histology will be confirmed by pathological experts.

### Objectives

The major objective is to assess the efficacy and safety of SJZD granules in the prevention and treatment of CRA post-polypectomy.

### Participants

Patients will be recruited from gastrointestinal endoscopy departments in 4 hospitals affiliated with Shanghai University of TCM, namely, Longhua Hospital, Yueyang Hospital of Integrated Traditional Chinese and Western Medicine, Shanghai Traditional Chinese Medicine-Integrated Hospital and Shanghai Municipal Hospital of Traditional Chinese Medicine.

#### Inclusion criteria

Participants will be eligible if they meet all of the following criteria:1. Individuals aged from 18 to 75 years, regardless of gender2. Individuals who underwent complete painless endoscopic adenoma resection (excluding hot polypectomy, hot snare polypectomy and argon plasma coagulation) within 2 weeks before recruitment3. At least 1 but no more than 6 CRAs confirmed by histology (including tubular, tubulovillous, and villous adenoma)4. Boston Bowel Preparation Scale (BBPS) score ≥7 points5. The score of SDS in TCM ≥20 points6. Individuals with adequate organ function7. Individuals who provide informed consent and can cooperate with long-term follow-up

#### Exclusion criteria

Participants will be excluded if they meet any of the following criteria:1. The adenoma was not completely removed in previous endoscopy2. Individuals who regularly take aspirin, non-steroidal anti-inflammatory drugs, cyclo-oxygenase 2 inhibitors, calcium or vitamin D and who receive long-term systemic immunotherapy3. Pregnant or lactating women4. Individuals with mental disorders or other conditions who are not able to cooperate5. Individuals who are unable to take drugs orally, lack physical integrity of the upper gastrointestinal tract, or have malabsorption syndrome and other diseases that investigators consider may interfere with gastrointestinal movement or absorption6. Individuals who are complicated with acute and chronic diseases, including severe cardiovascular, hepatic and renal diseases, or experience severe postoperative complications7. Other situations that investigators consider unsuitable for participation

#### Withdrawal/termination criteria

Participants will be withdrawn or terminated from the trial if they meet any of the following criteria:1. Serious adverse events are reported at any time, and patients are unable to continue2. Patients who present with serious changes or complications related to the disease during the trial3. Patients who cannot comply with the instructions and follow-up procedures of this trial, leading to incomplete medical administration records, or patients who took banned drugs or other medications that may interfere with the efficacy and safety evaluation of this study4. Patients who request to be withdrawn from the trial

Besides, researchers will record the last time of drug intake and collect evaluation items of participants who discontinue or deviate from intervention protocols.

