#### Concomitant treatment regulations

Other medical agents or interventions that may interfere with the evaluation of efficacy and safety in this study will be prohibited during the study. Participants who co-existed with other chronic diseases and need relevant treatments should record concomitant interventions in case report form (CRF).

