### Randomization and blinding

Permuted block randomization, which is stratified by recruiting sites, will be used to allocate participants to the SJZD group or placebo group in a 1:1 ratio by the SAS statistical analysis system. All drugs will be sealed in identical opaque envelopes only labeled with a random code number. Participants will be enrolled by clinicians and receive an envelope in sequence. An independent statistician will finish the randomization. Clinicians, nurses, researchers and patients who participate in this trial will all be blinded to the treatment assignment. The random number and treatment assignments will be sealed and reserved by the principal investigators of this study. The blinding will not be unmasked until the trial and data analysis finish or in the event of serious AEs. Emergency letters sealed in opaque envelopes will be sent to each recruiting site. Assignment information and emergent conditions are contained in the letter. If any serious AEs occur, the emergency letter will be opened, and the corresponding patient will be withdrawn from the trial. A report of serious AEs should be submitted to the principal investigators within 24 h. The codes of treatments will be uncovered after the closure of follow-up and the specific intervention relevant to the cords will be uncovered after data analysis.

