### Sample size

Based on a previous clinical trial, the effective rate of berberine, a famous Chinese medicine, in the prevention of CRA recurrence was 11% (Chen et al., 2020). The estimated effective rate of SJZD is 20% in this study. Following the 1:1 parallel control principle, SAS statistical analysis software was used to generate the sample size with a double-sided significance level of 0.05 and a power of 80% (α = 0.05, β = 0.2). Assuming that the dropout rate in each group was 10%, a requirement of 240 cases was determined (*n* = 120 in each group).

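### Withdrawal item 3 ends trial participation for non-adherent patients without securing the month-12 endoscopy that the intention-to-treat analysis needs

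*Protocol article*

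**What the plan says.** The Withdrawal/termination criteria section opens with a rule: "Participants will be withdrawn or terminated from the trial if they meet any of the following criteria". Item 3 has two triggers. One is non-adherence: "Patients who cannot comply with the instructions and follow-up procedures of this trial, leading to incomplete medical administration records". The other is medication: "patients who took banned drugs or other medications that may interfere with the efficacy and safety evaluation of this study". The section ends with a data-collection provision: "researchers will record the last time of drug intake and collect evaluation items of participants who discontinue or deviate from intervention protocols".

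Study design and setting fixes when the outcome is measured: "Endoscopy will be conducted at the end of the intervention phase and 1 year later". Table 2 agrees, with endoscopy at enrolment, Visit 4 (month 12) and Visit 5 only. Outcomes defines the primary outcome as adenoma recurrence at the first year after removal. Statistical analysis applies ITT to efficacy and safety and fills missing values by last observation carried forward (LOCF).

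**The concern.** Both triggers in item 3 occur after randomisation, and the stated consequence is leaving the trial, not only stopping study drug. ITT is most informative when every randomised patient's outcome is sought whatever happens to treatment. Here the first endoscopy after baseline is at month 12, so a patient who leaves before then may have no primary outcome observed, although the examination was already on the schedule.

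The loss need not be random. Adherence to twice-daily granules over 12 months could differ by arm. The article does not list the banned drugs. If they match the exclusion list (aspirin, NSAIDs, COX-2 inhibitors, calcium, vitamin D), they would include calcium and vitamin D, which the Discussion links to lower adenoma risk. Removal could then be related to the outcome. At stake is whether the primary comparison rests on observed or imputed results for these patients.

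**Working it through.** **Step 1: the texts side by side.**

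- Consequence of item 3: withdrawal or termination from the trial (opening sentence of the section).
- Data afterwards: last drug intake and evaluation items (closing sentence). No timing is given and endoscopy is not named.
- Primary outcome: recurrence at year 1, which needs the Visit 4 endoscopy (Outcomes; Table 2).
- Analysis: ITT with LOCF (Statistical analysis). No sentence drops withdrawn patients from the analysis set.

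A patient removed before month 12 therefore stays in the ITT count. Whether the result is observed depends on how a site reads the closing sentence: as one assessment at exit, or as continued attendance to Visit 4. On the first reading, LOCF has only the baseline state after complete resection to carry forward. That would probably be counted as no recurrence, but the article does not say so.

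**Step 2: what can be put in numbers.** The article gives no figure for item 3. The nearest is in Sample size: "Assuming that the dropout rate in each group was 10%, a requirement of 240 cases was determined". That is 0.10 × 120 = 12 patients per arm, leaving 108. This point does not depend on how the 240 was derived.

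Assumptions for an all-cause upper case at the planned dropout:

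- all 12 leave before Visit 4 without endoscopy;
- they have the same recurrence risk r as the others;
- r lies between the 26.6% and 51.6% quoted in the Discussion (follow-up times differ, so the top may be too high for month 12).

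Results per arm:

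- Unobserved share: 12/120 = 10 percentage points.
- Recurrences unseen, 12 × r: 12 × 0.266 = 3.2; 12 × 0.516 = 6.2.
- Arm rate if the 12 count as no recurrence, 108r/120: 23.9% and 46.4%.
- Arm rate if all 12 recur, (108r + 12)/120: 33.9% and 56.4%.
- Equal loss and equal risk in both arms, missing counted as no recurrence: observed difference = 0.9 × true difference.
- One extra patient lost from one arm, r/120: that arm's rate falls by 0.22 to 0.43 points.

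**Step 3: direction.** With no true effect and missing counted as no recurrence, the false difference (placebo minus SJZD) is r × (share lost on SJZD − share lost on placebo). The article gives no split by arm. If 15% were lost on SJZD and 5% on placebo (assumed), it would be 0.266 × 0.10 = 2.7 points to 0.516 × 0.10 = 5.2 points in favour of SJZD. Swapping the two shares gives the same size against SJZD. If the Visit 4 endoscopy is done in these patients, this bias is zero.

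**The case against.** The strongest reply is the closing sentence of the same section. A patient who takes a prohibited drug or does not follow dosing has deviated from the intervention, and the sentence says evaluation items will be collected from such patients. The article is also a condensed account of a fuller protocol (V2.0, mentioned under Ethics and dissemination), which may say what is collected and when. This has real force: it shows an intention to keep collecting data, and it rules out calling the text a flat contradiction of ITT. It does not dispose of the point, because the concern rests on a stated rule and not on an omission. The article says that these patients leave the trial, and the provision that follows does not clearly undo that.

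Other objections also stand. A reader might infer that item 3 patients are excluded from the analysis. The article does not support that: withdrawal from follow-up is not removal from the analysis set, and Statistical analysis keeps ITT with a rule for missing values. A reader might also take the 3.2 to 6.2 unseen recurrences, or the 10% shrinkage, as the effect of item 3. They are not: they describe all planned dropout, and the shrinkage also assumes an LOCF coding that the article does not state. That coding is a separate issue affecting every missed Visit 4. Finally, Randomization and blinding uses similar wording after a serious adverse event ("the emergency letter will be opened, and the corresponding patient will be withdrawn from the trial"). That is a safety provision with a different trigger and does not show what was intended for item 3.

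**Conclusion.** The point holds as a tension in the wording, with a practical consequence. Item 3 ends trial participation for events after randomisation, and the closing sentence does not secure the one examination that supplies the primary outcome. Patients removed before month 12 may therefore be analysed under ITT on an imputed result.

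The size and direction of any bias cannot be derived. The 12 patients per arm are a ceiling for loss from all causes if dropout runs as planned, and item 3's share is unknown. The possible effect runs from none, if sites still perform the Visit 4 endoscopy, to an unknown part of the all-cause figures above. Nothing in the article supports a claim that the rule favours SJZD. This is a correction worth making because it is cheap, not a defect that invalidates the design.

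**What to change.** Reword item 3 so that its events are recorded as protocol deviations that may lead to stopping study drug, with no automatic exit from the trial. Extend the closing sentence of Withdrawal/termination criteria to say that these patients keep the scheduled Visit 4 and Visit 5 endoscopies and spleen deficiency scales, and are analysed in the arm to which they were randomised, unless they withdraw consent.

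The cost is protocol wording, a note to the 4 sites, and notice to the ethics committee, which Ethics and dissemination says is informed of design changes. No examination is added: the endoscopies are already planned for every patient. Concomitant treatment is already recorded under Concomitant treatment regulations and in the Drug combination row of Table 2.

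There are two downsides. Off-plan drug use stays in the ITT estimate and may dilute it, or shift it if such use differs by arm. Some patients who cannot comply with follow-up will still be lost whatever the text says.

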### Interventions

#### Drug intervention

The intervention phase will last 12 months. Both SJZD and placebo are designed as granules with the same weight (1.77g/pack) and packaging. The appearance, texture, smell and taste of placebo granules are the same as SJZD granules but without any therapeutic effect. The granules in one package are dissolved in 200 mL of hot water. Patients are asked to take two packages orally two separate times in 1 day (3.54 g/day). There is no reduction or escalation of drug dose and frequency. SJZD and placebo are provided by Sichuan Neo-green Pharmaceutical Technology Development Co., Ltd. (Sichuan, China). The ingredients of placebo include one-tenth dose of SJZD (Radix ginseng, Rhizoma Atractylodis macrocephalae, Poria and Radix Glycyrrhizae Preparata) and maltodextrin. All the processing and preparation of medications and placebo are qualified. For participants who have severe adverse events (AEs) relevant to this trial, post-trial care will be arranged, and additional pecuniary compensation will be given. For participants who have adverse reactions not related to the drug in this trial, the relevant medical interventions will be implemented based on the comprehensive information of patients, including previous medical histories, symptoms and signs, laboratory, imaging and other examination results.

#### Concomitant treatment regulations

Other medical agents or interventions that may interfere with the evaluation of efficacy and safety in this study will be prohibited during the study. Participants who co-existed with other chronic diseases and need relevant treatments should record concomitant interventions in case report form (CRF).

#### Endoscopic procedures

At every recruiting site, specialists with substantial experience will perform the endoscopic examinations and polypectomies. The clinical practice follows the guideline published by The Japanese Society of Gastroenterology (JSGE) (Tanaka et al., 2021). Adequate bowel cleaning will be required to ensure clear observation of the entire colorectum. All detected adenomas or polyps will be photographed, and standard endoscopic reports will be submitted by the endoscopists and preserved by the principal investigators. Tissue will be collected and stored following the routine clinical care and regulations of the Department of Pathology.

### Outcomes

The primary outcome is the recurrence rate of CRA between the SJZD group and the placebo group at the first year after CRA removal. The number, size and location of adenomas will be recorded. Pathological type will also be recorded if recurrent adenomas meet the criteria for resection. Secondary outcomes include the following: 1) the recurrence rate of CRA at the second year post-polypectomy; 2) the pathological type of adenoma detected at either of the two endoscopies; and 3) the changes in spleen deficiency PRO scores after intervention.

Safety outcomes will comprise physical examinations, vital signs and laboratory examinations at every visit and AEs during the intervention phase. Laboratory indices will include routine blood tests, routine urine tests, routine stool tests, liver function tests, renal function tests and electrocardiograms. In the event of AEs, the onset time, symptoms and signs, duration of event and abnormal laboratory indicators or imaging results will be recorded. The definition and grade assessment of AEs are in accordance with the National Cancer Institute Common Terminology Criteria for Adverse Events (Version 5.0) (SERVICES USDOHAH, 2017).

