### Statistical analysis

SAS statistical software will be used to analyze the data. The efficacy and safety of this study will be analyzed by the principle of intention-to-treat (ITT). The missing data will be filled by the method of the last observation carried forward. The measurement data will be expressed as the mean ± standard deviation or median (quartile interval) determined by whether the data are normally distributed and the variance is uniform. χ^2^ tests will be used to compare the primary and secondary endpoints between the SJZD group and the placebo group. The paired *t*-test and independent sample *t*-test will be used for intragroup comparison and intergroup comparison, respectively. Logistic regression analysis will be used for the factors affecting the recurrence rate. Interim analysis will be arranged when 50% of the sample is collected. Sub-group analyses will be determined based on characteristics of participants such as gender, body mass index or previous history of gastrointestinal diseases. *p* < 0.05 is considered statistically significant.

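### Pathological type exists only for resected recurrences, so comparing it among those patients is not a randomised comparison; the article also leaves open how unresected lesions count in the primary

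*Protocol article*

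**What the plan says.** All references are to the protocol article.

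- **Primary outcome (Outcomes).** "The primary outcome is the recurrence rate of CRA between the SJZD group and the placebo group at the first year after CRA removal". No histological definition of a recurrence is attached.
- **Data on recurrent lesions (Outcomes).** "The number, size and location of adenomas will be recorded", with no condition. The next sentence is conditional: "Pathological type will also be recorded if recurrent adenomas meet the criteria for resection".
- **Schedule note (below Table 2).** It has the same structure: "Patients who are detected to find recurrence of colorectal adenoma and meet the criteria of resection are undergone endoscopy", followed by the statement that "histology will be confirmed by pathological experts".
- **Entry standard (Inclusion criteria, item 3).** "At least 1 but no more than 6 CRAs confirmed by histology (including tubular, tubulovillous, and villous adenoma".
- **Second secondary outcome (Outcomes).** "the pathological type of adenoma detected at either of the two endoscopies".
- **Test (Statistical analysis).** Chi-square "tests will be used to compare the primary and secondary endpoints between the SJZD group and the placebo group". Intention-to-treat is named as the general principle. No denominator or unit of analysis is given for pathological type.
- **Endoscopic procedures.** Every adenoma or polyp found is photographed, and practice follows an external guideline. The article does not reproduce resection criteria and does not mention histology for lesions left in place.

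**The concern.** There are two separate consequences of tying histology to resection.

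**Pathological type.** A patient without recurrence has no adenoma type, and a patient whose lesion was left in place has none on record. Recurrence and resection both happen after randomisation, and recurrence is what the treatment is meant to change. If the chi-square table contains only patients with a recorded type, the two columns are no longer comparable groups. A treatment that prevents mainly simple tubular adenomas would leave a smaller group with a higher villous share, and the table would read as harm. If adenomas rather than patients were counted, several lesions from one patient would also be treated as independent.

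**Primary outcome.** The label adenoma is applied at detection, before any pathology. The article does not say whether a lesion that is seen, not resected and never confirmed makes the patient a recurrence. If it does, non-adenomatous lesions would enter as events and pull the two arms together. If it does not, true adenomas left in place are lost. Either rule can be defended, but choosing after the data are seen cannot.

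**Working it through.** The article gives no figure of its own on this point, so there is nothing to reproduce directly. The check has a reading of the text and two illustrations.

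**1. Where histology exists.**

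| Stage | Called adenoma on the basis of | Histology on record |
|---|---|---|
| Entry | histological confirmation | always |
| Follow-up, lesion resected | detection, then pathology | yes |
| Follow-up, lesion not resected | detection | none stated |

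The third row is the gap. Outcomes and the schedule note both create it, and no section says how that row counts in the primary outcome.

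**2. Pathological type: constructed counts, 108 patients per arm.** Suppose treatment halves tubular-only recurrence and leaves villous histology unchanged.

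| | Placebo | SJZD |
|---|---|---|
| Worst histology villous | 14 | 14 |
| Tubular only | 40 | 20 |
| Any recurrence | 54 | 34 |
| Villous among recurrences | 14/54 = 26% | 14/34 = 41% |
| Villous among all patients | 14/108 = 13% | 14/108 = 13% |

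No patient is worse off, yet the within-recurrence table shows a 15-point excess of villous histology on SJZD. The subset would also be small and uneven. With a 40% placebo rate and a 20-point reduction it holds about 43 placebo and 22 SJZD patients if every recurrence is resected, and about 22 and 11 if half are.

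**3. Primary outcome: cost of each classification rule.** Inputs:

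- n = 108 per arm, from 120 × (1 − 0.10), the stated size less the stated dropout.
- Placebo rate p1 of 26.6% and 51.6%, the ends of the literature range in the Discussion. The Sample size section states no placebo rate.
- p2 = p1 − 0.20. This reads the 20% effective rate as an absolute reduction, which the article does not say.
- A 10% error rate in either direction, assumed.

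The Sample size section read literally, 11% against 20%, needs 253 per arm (564 in total after dropout), not 240. The power levels below are therefore illustrations and not properties of this plan. That mismatch is a separate matter.

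Power = Φ{[d − 1.96·√(2p̄(1−p̄)/n)] / √([p1(1−p1) + p2(1−p2)]/n)}, with d = p1 − p2 and p̄ the mean of the two rates.

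- Counting a share f of adenoma-free patients as recurrent: p′ = p + f(1 − p).
- Missing a share m of true recurrences: p′ = p(1 − m).

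With f or m at 10%, the 20-point difference shrinks to 18 points either way.

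| Placebo rate | No error | f = 10% | m = 10% |
|---|---|---|---|
| 26.6% vs 6.6% | 98% | 33.9% vs 15.9%: 87% | 23.9% vs 5.9%: 96% |
| 51.6% vs 31.6% | 85% | 56.4% vs 38.4%: 76% | 46.4% vs 28.4%: 78% |

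Worked case, 51.6% with f = 10%: p̄ = 0.474; null standard error √(2 × 0.474 × 0.526/108) = 0.068; alternative standard error 0.067; (0.180 − 1.96 × 0.068)/0.067 ≈ 0.70; Φ(0.70) ≈ 0.76.

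At f = 5% and 20%, power is 94% and 71% (26.6%), or 81% and 66% (51.6%).

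**The case against.** **A reader might infer that the primary outcome counts unconfirmed lesions as adenomas.** The documents do not support that as a fact. No section says an unresected lesion is an event. Histological tests are scheduled at Visits 4 and 5, with confirmation by pathology experts. It is equally unstated that such lesions are excluded. What stands is that the rule is missing.

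**The gap may be small in practice.** Endoscopy follows an external guideline that is not shown. If nearly every suspected adenoma is resected under it, few lesions lack histology. The documents give no share left in place, so this can be neither confirmed nor dismissed.

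**Denominator and unit for a secondary outcome often belong in the analysis plan.** This is fair. Intention-to-treat with a chi-square test is compatible with a per-patient table over everyone randomised. But the article itself limits when the variable exists, and read plainly its outcome is the type among adenomas found. The point is therefore a caution about the analysis this wording invites; it does not show that the wrong analysis has been fixed.

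**Blinding limits the harm to the primary.** Clinicians, researchers and patients are blinded, so misclassification would probably be similar in both arms. The likely effect is dilution and lost power, not a false claim of benefit.

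**Requiring confirmation has its own price.** This stands. At a 51.6% placebo rate, missing 10% of true recurrences costs about as much (85% to 78%) as wrongly counting 10% of adenoma-free patients (85% to 76%). It also makes the primary event depend on resection. The choice is a trade-off.

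**Conclusion.** The concern holds in two parts of unequal strength.

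The pathological-type part is the firmer one. By the article's own recording rule the variable is defined only after recurrence and resection, so a test among patients with a recorded type is not a randomised comparison. The 26% against 41% example shows the direction such a table can take. Its counts are constructed and predict nothing about this trial.

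The primary part is an unresolved definition: the text shows no error of counting. If unconfirmed lesions are counted, the expected consequence is dilution, probably similar in both arms. The power losses of roughly 9 to 11 points for 10% false events, and 2 to 7 points for 10% missed events, rest on an assumed 20-point reduction, 108 evaluable per arm, borrowed placebo rates and an assumed error share. The real size depends on how many recurrent lesions are left in place, which the documents do not give.

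**What to change.** 1. **Pathological type.** Analyse one value per patient over all randomised patients: worst histology, as none, tubular, or tubulovillous/villous. Keep any table restricted to recurrences, but label it descriptive. Patients whose only lesions were unresected should be placed by the same rule as in item 2.
2. **Primary outcome.** Before unblinding, write down how an unresected lesion counts. The preferable rule is histologically confirmed adenoma, which matches the entry standard. Report the alternative, counting unresected lesions as events, as a prespecified sensitivity analysis, and give the number of such lesions by arm.

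The cost is wording and programming. No change to endoscopic or pathological practice is needed. The downside is that true adenomas left in place would not count in the primary, which lowers the event rate and some power. The sensitivity analysis shows whether that matters.
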